#### Statistical Analysis Plan

The descriptive analyses outlined for Aim 1 will apply to Aim 2 as well. Regarding the IPTW, we will apply the same procedures as in Aim 1 to the dataset to obtain a weight for each woman. The effect of RT on mortality will be assessed via 5-year survival curves of the study population using the Kaplan-Meier method, which will incorporate the IPTW. To estimate the effect of RT and comorbidity on mortality, we will use the weighted Cox proportional hazards model to obtain the IPTW-adjusted relative hazard of 5-year overall and cause-specific mortality from the date of diagnosis. IPTW-adjusted subdistribution hazard ratios with 95% CIs will be reported. The proportional hazards assumption will be assessed using the Schoenfeld residuals test, which measures the correlation between residuals of each covariate and time and evaluates the interactions with time in the survival models. Sensitivity analysis will be performed to examine whether the censoring may be informative rather than noninformative. We will consider 2 extreme possibilities: events occurred immediately after censoring or later than any other observed events.

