**Methods:**

We will use a retrospective cohort study design with the population-based Surveillance, Epidemiology, and End-Results database linked to the Medicare Health Outcomes Survey (SEER-MHOS). Older women (≥65 years) who were diagnosed with low-risk breast cancer in 1998-2014, received breast-conserving surgery, and participated in MHOS 1998-2016 are eligible for this analysis. The latent class analysis clustering method will be used to identify each patient’s prediagnosis comorbidity burden, and HRQOL will be evaluated using the Short Form 36/Veterans RAND 12-Item Health Survey scales. The inverse-weighted estimates of the probability of treatment will be included to control for treatment selection bias and confounding effects in subsequent analysis. The association of RT with HRQOL trajectory will be evaluated using inverse-weighted multilevel growth mixture models. The inverse-weighted Cox regression model will be used to obtain hazard ratios with 95% CIs for the association of RT with survival outcomes. Differential effects of RT on both outcomes according to comorbidity burden class will also be evaluated.

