Despite the aforementioned guideline update, the treatments of older women with low-risk breast cancer vary widely. In prior studies, the patterns of RT omission were not consistent across institutions, even at NCCN member institutions [11-13]. More importantly, RT usage in this group of women still exceeds 50% [14]. A recent survey reported that high proportions of surgeons and radiation oncologists erroneously overestimated survival benefits associated with RT in this group of women [15] because the estimation of life expectancy in older women is not straightforward [11]. Many treatment-decision algorithms include age to estimate life expectancy, but chronological age is not always correlated with one’s biological age and mortality. Including geriatric assessment in the algorithm improved compliance with NCCN guidelines without diminishing survival benefits [16]. Since accompanying comorbid conditions at diagnosis are strongly associated with mortality regardless of age [17-19], considering comorbidity burden in addition to age and tumor characteristics will improve the selection of women who can omit RT.

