#### Measurements

The exposure variables are the same as those of Aim 1, namely BCS alone and BCS with adjuvant RT. We will consider vital status and cause of death as the outcomes. The main outcome for Aim 2 will be mortality (all-cause mortality and breast cancer-specific mortality considering nonbreast cancer mortality as a competing event). The SEER data file provides the vital status of participants and the date and causes of death, which have been verified through the National Death Index. Survival will be calculated from the date of diagnosis to the last known follow-up date or December 31, 2016, whichever comes first. As in the case of Aim 1, the comorbidity burden will serve as the effect modifier. The confounding factors will match those of Aim 1.

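### Aim 2 describes a weighted Cox model but reports only subdistribution hazard ratios: no model is named that yields them, and alone they can misstate the comorbidity effect on breast cancer death

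*Protocol article*

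**What the plan says.** The Aim 2 Measurements section sets the outcome as "all-cause mortality and breast cancer-specific mortality considering nonbreast cancer mortality as a competing event". The Aim 2 Statistical Analysis Plan then names one regression model: "we will use the weighted Cox proportional hazards model to obtain the IPTW-adjusted relative hazard of 5-year overall and cause-specific mortality". The next sentence gives the effect measure: "IPTW-adjusted subdistribution hazard ratios with 95% CIs will be reported". That sentence is not restricted to one of the two outcomes.

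Elsewhere only Cox regression is mentioned. The abstract describes the output as ordinary hazard ratios: "The inverse-weighted Cox regression model will be used to obtain hazard ratios with 95% CIs for the association of RT with survival outcomes". The Aim 2 paragraph of the Introduction and the legend of Figure 1 also name only an IPTW-adjusted Cox model. The one curve method is weighted Kaplan-Meier ("5-year survival curves of the study population using the Kaplan-Meier method, which will incorporate the IPTW"). Neither a Fine-Gray model nor a cumulative incidence function appears.

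The regression has two targets ("To estimate the effect of RT and comorbidity on mortality"), and comorbidity burden class is also the effect modifier.

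**The concern.** A Cox model for breast cancer death that censors other deaths gives a cause-specific hazard ratio: the relative rate of breast cancer death among women still alive. An SHR comes from a different model, which keeps women who have died of other causes in the risk set and describes the effect on cumulative incidence. The plan describes the first kind of model and promises the second kind of result. An analyst could defend either, and the choice could be made after both had been seen.

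The choice matters most for comorbidity. The Introduction itself says that "accompanying comorbid conditions at diagnosis are strongly associated with mortality regardless of age". A factor that raises other-cause death lowers the cumulative incidence of breast cancer death even if it leaves the rate of breast cancer death unchanged. With the SHR as the only reported ratio, women with high comorbidity could appear protected from breast cancer death merely because more of them die of something else first.

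**Working it through.** The article gives no event counts, death rates or expected effect sizes for Aim 2, so it has no figure to reproduce. The check sets the statements side by side and then illustrates the gap under assumed rates.

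**1. Model against measure**

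| Outcome | What the described Cox model gives | What the reporting sentence promises |
|---|---|---|
| Overall mortality | Ordinary HR | SHR; no competing event, so identical to the HR |
| Breast cancer death | Cause-specific HR, if other deaths are censored | SHR; needs a subdistribution model, none named |

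Overall-mortality results are therefore unaffected, and the label is merely uninformative. The mismatch has consequences only for breast cancer death.

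**2. Formulas.** With constant breast cancer hazard h1 and other-cause hazard h2, the cumulative incidence of breast cancer death is

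CIF(t) = h1/(h1+h2) × [1 − exp(−(h1+h2)t)].

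The SHR is summarised by the ratio of cumulative subdistribution hazards at t = 5 years, ln(1−CIF_a)/ln(1−CIF_b).

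**3. Comorbidity contrast.** Assumptions, not from the documents: h1 = 0.005 a year in every class, so the true cause-specific HR is 1.0; h2 = 0.015 in the lowest class; h2 in the highest class varied.

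- Lowest class: CIF = 0.005/0.020 × (1 − e^−0.100) = 0.02379; −ln(1−CIF) = 0.02408.
- Highest class, h2 = 0.12: CIF = 0.005/0.125 × (1 − e^−0.625) = 0.01859; −ln(1−CIF) = 0.01876.
- SHR = 0.01876/0.02408 = 0.78.

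| Other-cause hazard, highest class (per year) | True cause-specific HR | 5-year SHR, highest vs lowest |
|---|---|---|
| 12% | 1.0 | 0.78 |
| 6% | 1.0 | 0.90 |
| 3% | 1.0 | 0.96 |

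A simulation of the 12% case (4 million women, complete follow-up to 5 years) gave about 1.00 from Cox with other deaths censored, and 0.78 when women who died of other causes were kept at risk.

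**4. RT contrast.** Same class hazards; the last two rows assume other-cause mortality 30% lower in RT women within each class after weighting.

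| True cause-specific RT HR | Other-cause ratio, RT vs no RT | SHR, lowest class | SHR, highest class (12%) |
|---|---|---|---|
| 0.70 | 1.0 | 0.70 | 0.70 |
| 0.70 | 0.7 | 0.71 | 0.76 |
| 1.0 | 0.7 | 1.01 | 1.09 |

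If other-cause mortality is equal between RT groups, the RT ratio barely moves.

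**5. Scale against precision.** Multiplying the planned 634 women by the two CIFs above gives 634 × 0.01859 = 12 to 634 × 0.02379 = 15 breast cancer deaths in 5 years. With 15 deaths split evenly between RT groups, SE(log HR) = √(1/7.5 + 1/7.5) = 0.52. A ratio of 0.71 would then have a 95% CI of about 0.26 to 1.95, before any split by class. The difference between 0.71 and 0.76 is far below that resolution.

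**The case against.** The best defence is that a Fine-Gray analysis was intended. The Measurements section treats other deaths as competing events, Fine-Gray is a proportional hazards regression of Cox type, and the term cause-specific may describe the endpoint rather than the type of hazard. The SHR is a legitimate measure of effect on cumulative incidence, and absolute risk is relevant to the shared decision making that the article aims to support. All of this stands as an account of what may have been meant. It does not settle what the text says: on that reading the model sentence is the one to correct, and the abstract still promises ordinary hazard ratios from Cox regression.

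A reader might go further and infer three things that the documents do not support.

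- That an SHR is undefined for overall mortality. It reduces to the ordinary HR, so no overall-mortality result changes.
- That the SHR is simply the wrong measure. The article never says whether it wants the effect on the rate or on the cumulative incidence of breast cancer death, so the SHR cannot be called an error. The problem is that it stands alone and its model is not named.
- That the plan would manufacture the hypothesised RT-by-comorbidity interaction. That needs residual selection within class after weighting, which would also bias the overall-mortality results. The resulting drift is small beside the likely precision. The stated hypothesis moreover concerns 5-year mortality and survival in general, not breast cancer death in particular.

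**Conclusion.** The point holds as a mismatch between the model described and the only effect measure promised, with practical consequences for breast cancer death alone. The main risk is to the comorbidity effect: an SHR reported without its cause-specific counterpart could make high comorbidity look protective. The 5-year illustration runs from 0.96 to 0.78 for a true cause-specific ratio of 1.0. It rests on constant hazards, an assumed breast cancer hazard of 0.5% a year, and assumed other-cause hazards of 1.5% in the lowest class and 3% to 12% in the highest. The 0.78 figure needs an eightfold difference in other-cause hazard between classes. The direction follows from the article's own statement that comorbidity is strongly related to mortality; the size cannot be fixed from the documents. Any effect on the RT ratio is conditional on unequal other-cause mortality after weighting, and is modest.

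**What to change.** In the Aim 2 Statistical Analysis Plan, replace the sentence on subdistribution hazard ratios with the following:

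- For overall mortality, report the IPTW-weighted Cox HR.
- For breast cancer death, report the weighted cause-specific HR, with other deaths censored, for the RT, comorbidity and RT-by-comorbidity effects. Give the cause-specific HR for non-breast-cancer death beside it, so that a reader can see how far competing deaths drive any difference in cumulative incidence.
- If an SHR is kept, limit it to breast cancer death, name the weighted Fine-Gray model that produces it, and interpret it as an effect on cumulative incidence.

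The cost is a few sentences and one extra model on data already held. The survival results were scheduled for submission in June 2021, after the analysis start of November 2020 given in the article, so the wording could be settled before those results are produced.

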### Limitations

A significant limitation of this study concerns the lack of data on chemotherapy, endocrine therapy, or other systemic therapy information from the SEER data, which may have a major impact on HRQOL and survival outcomes. To minimize the confounding effects from other treatments on HRQOL, we restricted our study population to women with low-risk, favorable breast cancer whose treatment plan would typically not involve chemotherapy. We assumed that most women in the study population received endocrine therapy according to their ER-positive status. Another limitation concerns the SEER-MHOS data; although they are population-based data, SEER covers certain geographic areas, and MHOS only samples insured women; thus, the overlapping of the 2 databases could be very limited, and only some women/tumor characteristics will be considered in the analysis. However, to the best of our knowledge, this is the best resource to evaluate the long-term effect on HRQOL from RT at the population level.

## Results

As of October 2020, the study was approved by the Institutional Review Board of the University of Central Florida (SBE-18-14238), and the permission to use the SEER-MHOS database was obtained from NCI and SEER. Data have been curated for data analysis, women with low-risk breast cancer who met the inclusion and exclusion criteria have been identified, and prediagnosis comorbidity burden class has been characterized by latent class analysis. Further data analysis will begin in November 2020. The results of this study will be disseminated in peer-reviewed journals and presented at medical/scientific conferences. The first set of results of this study, namely those concerning prediagnosis comorbidity burden and HRQOL, will be submitted for publication in peer-reviewed journals in February 2021, and the second set of results regarding the effect of RT on survival outcomes will be submitted in June 2021.

## Discussion

This study will provide empirical evidence for the effect of RT on HRQOL trajectory as well as survival outcomes using comparative effectiveness research methods with patient-reported HRQOL outcomes, which provide patients’ perspectives on health care options. This research has the potential to improve clinical outcomes of older women with cancer enrolled in Medicare Advantage Organizations by providing information on HRQOL trajectories in addition to potential survival advantages from RT. This project will contribute new knowledge of long-term HRQOL to the existing evidence concerning the use of adjuvant RT after BCS in older women with low-risk breast cancer. By examining the independent and potential interactive effects of RT and comorbidity on HRQOL trajectories and survival outcomes, this evidence can facilitate communication between older women and their health care providers for shared decision making.

### Data Statement

The data analyzed in this study are available in the NCI’s repository [45]. Permission to use the data is required by the NCI. Investigators interested in using SEER-MHOS data must submit a research protocol as part of their data request.

## Abbreviations

BCS: breast-conserving surgery
ER: estrogen receptor
HRQOL: health-related quality of life
IPTW: inverse probability of treatment weighting
MHOS: Medicare Health Outcomes Survey
NCCN: National Comprehensive Cancer Network
NCI: National Cancer Institute
RCT: randomized controlled trial
RT: radiation therapy
SEER: Surveillance, Epidemiology, and End Results
